## **1. Summary of the research plan**

**Background:** A patients' decision regarding "Do Not Resuscitate" (DNR) code status, which is a legal order to withhold cardiopulmonary resuscitation (CPR) or advanced cardiac life support in respect of a patient's wish in case of a cardiac arrest or respiratory failure, has important medical and socioeconomic consequences. Yet, hospitalized patients often have insufficient information about expected outcomes from resuscitation measures. Research shows that <20% of in-hospital patients, who require CPR survive and subsequently many have permanent brain damage or disability. Although challenging in clinical routine, sharing information about expected prognosis with patients is a prerequisite for informed decision-making. In a recent hospital-based survey we found that DNR discussions are often insufficient with physicians not actively involving patients in the decision-making process, but relying decisions on the presumed preferences without in-depth discussions of patients' choices and consequences.

**General aim:** This trial is designed to investigate whether checklist-guided shared decision-making including decision aids and communication of expected outcome influences patients' decision regarding DNR code status, and at the same time, improves decision-making quality as judged by patient's decisional comfort, patient knowledge and involvement in decision-making and patient satisfaction.

**Patient population:** Consecutive adult medical patients admitted for in-hospital care, independent of medical diagnosis are eligible. Patients unable to complete questionnaires or unable to follow code status discussions (e.g., due to cognitive impairment such as dementia or delirium) and patients in whom resuscitation efforts are deemed futile are excluded.

**Methods:** multicenter, cluster randomized controlled trial involving six Swiss teaching hospitals.

**Intervention:** Medical residents conducting code status discussions will be randomized by an electronic, web-based system to the intervention group with shared decision-making facilitated by a checklist and a decision aid or to the usual care group. The decision aid was developed during a consensus conference, in which feedback from patients and clinicians was sought and integrated, and later field-tested until thematic saturation was achieved. Intervention group residents will receive detailed instructions about the shared decision-making checklist with specific communication teachings. To reduce bias, control group residents will also receive information about the importance of code status discussions and a general communication training, but no teaching regarding shared decision-making and no checklist will be used.

**Endpoints:** The primary outcome is the frequency of DNR code status among patients per resident (i.e., patients choosing that CPR and intubation measures should not be performed in case of acute deterioration). Our key secondary endpoint is the quality of decision-making as judged by patient's decisional comfort assessed through the validated German translation of the Decision Conflict Scale. Additionally, we will investigate patient's knowledge about resuscitation measures and expected outcome, patients' involvement in the shared decision-making process assessed through the validated German translation of the SDM-q-9 questionnaire, patients' concerns and fears and overall satisfaction with the code status discussion, as well as physicians perceived comfort with patient's choice and satisfaction with code status discussion. At hospital discharge, we will assess length of hospital stay, ICU-admissions, in-hospital resuscitations, through medical chart review.

**Sample size and statistics:** Based on pilot data in this patient population, we expect that 30% of patients in the usual care control will have a DNR code status, which will increase to 45% in the intervention group. We plan to include 174 residents (cluster) with a mean of 5 eligible patients per week over a 3-week period (total of 15 patients per cluster) in the five participating centers over a total study time of 2 years. Based on these assumptions, we aim to include 2610 patients among 174 residents, which will give this study an 80% power at a 0.05 alpha error with an inter-cluster correlation of 0.5.

**Discussion:** Although code status discussions are a cornerstone of patient-centered care, there is a lack of trials investigating the most appropriate approach for physicians to communicate with patients about their preference. This multicenter randomized-controlled trial will close this important knowledge gap by

### *Study protocol and statistical analysis plan*

systematically investigating effects of checklist-guided shared decision-making on patients' decisions regarding DNR status and the quality of decision-making.

## **2. Research plan**

### **2.1. Current state of research in the field**

Patient-centered care has become an important ethical principle in clinical practice over the last decades. The American Institute of Medicine considers patient-centered care as a key element of high-quality care[1]. Patients are seen as partners with healthcare professionals and their individual needs and health outcomes are the main focus in patient-centered care. Not only clinical markers but also psychological, emotional needs are of major importance in this context. Herein, a cornerstone of patient-centered care is the conversation with a patient about the preference of his code status. Informing patients about their choices of treatment, especially in elderly polymorbid patients, is acknowledged as an essential component of high-quality medical care[2-4]. Specifically, a patient's decision regarding "Do Not Resuscitate" (DNR) code status, which is a legal order to withhold cardiopulmonary resuscitation (CPR) or advanced cardiac life support (ACLS) in respect of the wishes of a patient in case their heart was to stop, or they were to stop breathing, has important medical and socioeconomic consequences. Research suggests that patients favor to be involved in medical decisions regarding their care at the end of life[5-8]. Still, although recommended by the Swiss Academy for Medical Sciences, such DNR discussions are often insufficient in clinical routine. In fact, in a recent survey focusing on code status discussions in Swiss hospitals we found that more than 60% of the surveyed patients reported that they do not recall such discussions, reflecting a deficiency in the quality of communication (Manuscript submitted for publication). In addition, research found that physicians often omit to describe resuscitation measures like chest compression or mechanical ventilation[9]. Although CPR is an invasive procedure with potential complications and research showing that less than 20% of in-hospital patients, who require CPR will survive and many have permanent brain damage or disability, risks and benefits are often not communicated with patients[10, 11], leading to misconceptions about CPR and expected outcome[12, 13]. Especially patients with low health literacy, who have difficulties to understand medical coherences, need improvements in communication to empower well-informed decision-making regarding code status.

There are several challenges to the current practice of code status discussions. First, these discussions are complex as objective medical facts and personal perspectives of physicians and patients both need to be integrated in the communication. Second, several studies found code status discussions to be ineffective due to poor communication skills of physicians[14, 15], which is particularly true for inexperienced residents[16]. Code status discussions are often conducted in a non-personalized way, missing the chance to focus on patients' values and goals[17]. Insufficient time during patient encounters pose an additional barrier for optimal communication[18-20]. Furthermore, the decision-making during code status discussions is often challenged by uncertainty around interventions and therapies that might be available, but whose outcomes remain uncertain[21, 22].

Importantly, patients with in-hospital cardiac arrests have a poor prognosis with a survival to hospital discharge rate of less than 20%[23, 24]. Furthermore, 40% of survivors suffer from substantial neurologic

deficits limiting their possibility to live an independent life[25]. In 2012, a British multi-center cohort study investigated medical charts of patients that had undergone resuscitation of an in-hospital cardiac arrest[26]. In more than 75% of patients that received CPR, the code status was unknown and 67% of patients that were resuscitated, actually had an underlying pre-existing fatal disease. Importantly, an independent assessment of all cases found that a DNR status would have been appropriate in 85% of cases, because the risk / benefit ratio was unfavourable for the patient, indicating medical futility. In addition, a recent cancer study shows that physicians often rather document a presumed code status, than conduct a discussion, leading to a high proportion of full code status despite severe illnesses of a patient [27]. Almost a third of patients that were presumably documented as full code would have preferred DNR code status[27].

Some previous studies aimed to improve code status discussions by investigating different communication elements. However, most studies that investigated different approaches to improve communication were observational and some relied on physicians rating of their own performance[28-31]. Other studies focused on patients with life-sustaining therapy in ICU settings, with a focus on end-of-life decisions like withdrawal of therapy [32, 33]. Thus, little is known about how to best communicate with polymorbid patients, where death is not imminent. Moreover, interventions were often complex, limiting clinical practicability. Best results regarding patients' knowledge of resuscitation were found in studies that used short videos about CPR as decision aids[34-37]. Although videos seem to increase patients' knowledge effectively and may therefore facilitate end-of life discussions, their practicality in elderly, polymorbid patients is unclear and they do not allow for personalized decisions. Importantly, most studies that investigated different approaches to facilitate code status discussions focused on terminally ill patients, suffering from advanced cancer stages or other palliative diseases. Still, due to its unpredictable nature, code status discussions are important for all patients admitted to hospital as cardiopulmonary arrest occurs in almost 1 per 1000 hospitalization days[38]. Above all, despite all research efforts, physicians' common practice to determine a presumed code status without prior discussion has not changed over the last 20 years, when an American trial, which investigated different approaches to improve care for seriously ill patients, pointed out this deficiency of medical practice[39].

In recent years, shared decision-making has become the standard for communication in situations of equal treatment options (equipoise). The goal of shared decision-making is to inform patients with best possible evidence and consider their perceptions and preferences. Through this process, the informed patient is empowered to weigh the different treatment options and influence medical decisions actively. Studies found that shared decision-making leads to higher satisfaction rates and increases self-responsibility of patients[40]. A recent randomized trial compared the effectiveness of shared decision-making with usual care in choice of admission for observation and further cardiac testing or for referral to outpatient evaluation in patients with chest pain and possible ischemic heart disease[40]. The trial found that shared decision-making, facilitated by the use of a decision aid, increased patient knowledge about their risk, increased engagement, reduced decisional conflict and safely decreased the rate of admission to an observation unit for further cardiac testing. Importantly, there is a relevant lack of trials looking at the effects of shared

decision-making in the setting of code status discussions (with patients in whom resuscitation is an option, i.e. who are not medically futile). Herein, we hypothesize that checklist-guided shared decision-making compared to routine will increase the frequency of patients choosing DNR code status. We also hypothesize that the intervention will not increase fear or dissatisfaction, but will lead to a higher comfort with the code status choice, improve satisfaction of patients across different quality dimensions and knowledge regarding resuscitation

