- c) Patients' concerns and fears brought up by the resuscitation discussion: Specifically, we will assess the following dimensions: (1) disturbance caused by the discussion, (2) fear of suffering from an actual cardiac arrest, (3) fear of suffering from a life-threatening disease (4) perceived feeling of being put under pressure during discussion; each of them rated on a VAS (0-10).
- d) Patients' satisfaction and perceived overall quality of the code status discussions: Specifically, we will focus on the following dimensions, each rated on a VAS (0-10): (1) overall satisfaction with resuscitation discussion; (2) perceived transparency of the discussion; (3) comprehensibility of the medical information regarding a resuscitation process and measures; (4) how well resuscitation options were elucidated

2. Physician- associated outcomes

- a) Perception of the physician with the resuscitation discussion: Specifically, perceptions will be assessed for both study groups separately in regard to the following dimensions: (1) satisfaction with resuscitation discussion and self-confidence during the discussion, each rated on a VAS (0-10); (2) perceived time management of the discussion, rated on a VAS (0-10)
- b) Surprise question to identify patients at risk of death within the next 12 months

3. Documented results in Database after 30 days

Database assessment after 30 days: Specifically, we are interested in (1) length of stay; (2) number of ICU admissions; (3) number of re-admissions to the hospital; (4) 30d mortality

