## *Study protocol and statistical analysis plan*

We will use cluster specific methods because residents rather than patients are randomized, and we expected that variance in how patients are managed would be partly explained by the resident. We will further account for the level of the participating center (hospital), as DNR discussions may vary according to study center. For each of the outcome measures we will test the null hypothesis that the likelihood of the outcome is the same in both study groups after accounting for some baseline characteristics (i.e., age, gender, main medical diagnosis). We will use hierarchical logistic regression to test for an effect of the intervention on any binary outcome measures and linear regression for any continuous outcome measure.

All analyses will be conducted using Stata. All analyses were performed using STATA 15.1 (Stata Corp, College Station, TX). For all analyses, we accept a type I error rate of  $\alpha = 5\%$ .

The design of our study and statistical approach was developed in close collaboration with statisticians and epidemiologists of the Clinical Trial Unit (CTU) of the University Hospital Basel.

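### The hypothesis that fear does not rise has no matching decision rule: a test of equality on the four concern and fear items cannot support it

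*Combined protocol and SAP*

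**What the plan says.** The hypotheses close section 2.1. After predicting more DNR choices, the protocol adds: "We also hypothesize that the intervention will not increase fear or dissatisfaction". The same sentence then predicts that the intervention will "improve satisfaction of patients across different quality dimensions and knowledge regarding resuscitation". Fear therefore carries only a no-increase hypothesis, while satisfaction carries a hypothesis of improvement as well.

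Section 2.2.8 lists the measures among the additional secondary endpoints. Under patients' concerns and fears there are four items: disturbance caused by the discussion, fear of a cardiac arrest, fear of a life-threatening disease, and "perceived feeling of being put under pressure during discussion; each of them rated on a VAS (0-10"). Satisfaction and perceived quality have four further items on the same scale.

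Section 2.3.9 gives one rule for all of them: "For each of the outcome measures we will test the null hypothesis that the likelihood of the outcome is the same in both study groups". The comparison is adjusted for a few baseline variables. The model is hierarchical logistic regression for binary outcomes and "linear regression for any continuous outcome measure". On error control it says "For all analyses, we accept a type I error rate of" 5%, without stating whether tests are one- or two-sided.

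The documents contain no non-inferiority or equivalence margin, no confidence-limit criterion and no power statement for the fear or satisfaction items. They do not say how a non-significant difference on these items will be interpreted.

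**The concern.** With equality as the null, the hypothesised result for fear can appear only as a failure to reject, or as a significant fall, which the protocol does not predict. Failure to reject is compatible with no rise, with a small rise, and, if the estimate is imprecise, with a rise that patients would notice. The test has no feature that separates these cases.

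The hypothesis matters to how the trial will be understood. The intervention is expected to raise DNR choices from 30% to 45%, and it uses images of simulated CPR and of a ventilated patient. Section 2.2.7 reports that patients were shown the decision aid to see whether it would cause discomfort. Readers will want to know whether disturbance, fear or a sense of pressure rose, and the plan as written gives no analysis that could support the answer it predicts.

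**Working it through.** **Inputs from the documents.** DNR rates of 30% and 45%, 80% power, alpha 0.05, intra-cluster correlation (ICC) 0.5, 15 patients per resident, 174 residents, 2610 patients (section 2.3.10); 1:1 allocation (section 2.2.5).

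**Inputs assumed.** SD of each scale 2.0, 2.5 or 3.0; ICC of the scale scores equal to the protocol's 0.5, with 0.05 as a low alternative; every questionnaire completed; normal approximation; two-sided 5% test; clustering by resident accounted for.

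**1. The plan's own figure.** Two proportions, pooled variance, no continuity correction, two-sided:

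n per arm = [1.96 × √(2 × 0.375 × 0.625) + 0.8416 × √(0.30 × 0.70 + 0.45 × 0.55)]² / 0.15² = 162.3, so 163.

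Design effect = 1 + (15 − 1) × 0.5 = 8. Then 163 × 8 = 1304 per arm, 2608 in total, or 87 residents per arm and 174 overall. The stated size reproduces, but it was set for DNR status only. A one-sided test would give 2048 patients, so the planned test appears to be two-sided.

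**2. Precision for a fear item.** SE = SD × √(2 × 8 / 1305) = SD × 0.1107.

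**3. Chance that a true rise δ is non-significant.** Approximately Φ(1.96 − δ/SE); the other tail is negligible.

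| SD | SE | 95% CI half-width | Non-significant, δ = 0.5 | Non-significant, δ = 1.0 |
|---|---|---|---|---|
| 2.0 | 0.221 | 0.43 | 38% | 0.5% |
| 2.5 | 0.277 | 0.54 | 56% | 5% |
| 3.0 | 0.332 | 0.65 | 68% | 15% |

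With half of the questionnaires completed, the δ = 0.5 column becomes 41%, 58% and 69%. At an ICC of 0.5 most of the variance comes from the number of residents, so response matters little.

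**4. A lower ICC.** At ICC 0.05 with all 174 residents, the design effect is 1 + 14 × 0.05 = 1.7 and the δ = 0.5 figures fall to 0.2%, 2.5% and 10%. However, section 2.3.10 allows the total sample to be adjusted to the ICC of code status decisions, estimated after 30 residents. If that were 0.05, the plan's formula needs 163 × 1.7 = 277 patients per arm, or 277 / 15 = 18.5, so 19 residents per arm and 38 in all (285 patients per arm). If the scale ICC is also 0.05:

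- SD 3: SE = 3 × √(2 × 1.7 / 285) = 0.328, and Φ(1.96 − 0.5/0.328) is about 67%.
- SD 2: SE = 2 × √(2 × 1.7 / 285) = 0.218, and Φ(1.96 − 0.5/0.218) is about 37%.

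A low ICC therefore helps only if the sample is not reduced in response to it.

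**5. What a margin rule would achieve.** With a true difference of 0 and the upper limit of the two-sided 95% CI compared with a margin m, power = Φ(m/SE − 1.96). At ICC 0.5 and 174 residents:

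| Illustrative margin | SD 2.0 | SD 2.5 | SD 3.0 |
|---|---|---|---|
| 0.5 points | 62% | 44% | 33% |
| 1.0 point | 99% | 95% | 85% |

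For 80% power at a 0.5-point margin, the total would be 4032, 6288 or 9056 patients. Neither margin comes from the documents.

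**The case against.** The best case for the plan is that these are minor outcomes described in ordinary language. The sentence stands in the background section. The aims in section 2.2.1 name DNR status, decisional comfort, knowledge, involvement and satisfaction, but not fear. Decisional conflict is the key secondary endpoint, and the fear items sit among many unpowered additional endpoints. This stands, and it limits the severity. It does not supply the missing rule: the no-increase statement is still a stated hypothesis, and section 2.3.9 applies its equality null to each outcome without exception.

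Four stronger readings are tempting and should not be drawn.

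- *A non-significant p-value will be presented as proof of no harm.* A reader might infer this, but nothing in the documents says so. They give no interpretation at all.
- *The fear items are the trial's designated check that extra DNR choices do not come at the price of distress.* No section gives them that role.
- *Satisfaction has the same gap.* It mostly does not. Improvement is predicted in the same sentence, an equality test suits that prediction, and a demonstrated improvement would settle the question of dissatisfaction without a margin.
- *With weak clustering, a trivial rise would be declared harm.* At ICC 0.05, SD 3 and all 174 residents, a 0.3-point rise would be significant about half the time. If the sample were cut to 38 residents under section 2.3.10, the figure is about 15%, since Φ(0.3/0.328 − 1.96) = Φ(−1.05). The higher figure needs a low ICC for the scales while the ICC for code status stays high. In any case, small effects reaching significance in a large sample is a general property of testing, not a fault of this plan.

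It is also fair to object that the SD and ICC of the scales are not documented, and that completion depends on patient consent (section 2.2.4). The percentages are therefore illustrations over a range. The logical gap does not depend on them.

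**Conclusion.** The point holds for the four concern and fear items. The protocol states a no-increase hypothesis for fear, and the only planned inference cannot support it. On the stated assumptions (SD 2 to 3, ICC 0.5, 174 residents, full completion), a true 0.5-point rise would go undetected about 38% to 68% of the time. A true 1-point rise would be missed 0.5% to 15% of the time, so the gap matters most for modest rises. How misleading a null result would be depends on the SD, ICC, response and margin, none of which the documents give for these scales.

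This is a should-fix matter. The analyses of DNR status and of decisional conflict are unaffected.

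**What to change.** In section 2.3.9, for the four concern and fear items:

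- Report the resident-clustered difference between groups with its two-sided 95% confidence interval.
- Conclude that the item was *not increased* only if the upper limit lies below a margin that the sponsor justifies and fixes before unblinding. Otherwise conclude *not shown*.
- If no margin can be justified, remove the no-increase claim and report the estimates with 95% confidence intervals only.

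Satisfaction keeps its test for improvement. The same interval rule, with the direction reversed, applies only if improvement is not shown.

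The cost is SAP wording and agreement on a margin, with no new data collection. The drawback is that a tight margin may leave the result inconclusive: at 0.5 points and ICC 0.5, power is only about 33% to 62%. A wider margin would be easier to meet but must be defended on its meaning to patients, not chosen because the sample can deliver it.
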